## Methods

### Study design

This is a single-blinded, two-arm RCT comparing the effects of an intervention video against a control video. We plan to recruit 446 adult Australian men to be randomised, with a 1:1 allocation (223 participants per arm).

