### Study setting

This study will be conducted entirely online. Participants will be recruited across Australia, with no geographical restrictions. They will attend an orientation session with up to nine other participants via the online web conferencing software, Zoom.

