### Participant selection

When participants register their initial interest in participating in the RCT via a registration website, they will be sent a detailed Plain Language Statement (PLS) outlining the requirements of trial participation. They must then attend an online orientation session run by one of our researchers and a study psychologist. In these sessions, the researcher will reiterate key background information from the PLS and answer questions to allow participants to provide informed consent. Once participants have had their questions answered, they will complete an online consent form, ticking a box to provide consent to continue to the T1 questionnaire (note that this includes consent to use of de-identified data for additional studies with ethical approval). If they do not consent, they will not proceed to the T1 questionnaire. The Depression Symptom Inventory—Suicidality Subscale (DSI-SS) [12] suicide risk screening questionnaire will be included in the T1 questionnaire. The study psychologist who attends the session will phone any participant who scores 2 or above on the DSI-SS to further assess their risk and to assist the participant in seeking further mental health support if the participant would like it. If the psychologist determines that the participant is at imminent risk of suicide or could be harmed by further participation, they will be excluded from further participation and referred for mental health support. If the participant is not determined to be at risk of harm, they will continue in the trial, but may still be referred for further support as required. The study psychologist will conduct a risk assessment using criteria such as whether the person has a current plan for suicide, and whether they have a history of suicide attempt. Participants will also be supplied with the psychologist’s contact details and able to contact them directly for further support for up to 4 weeks following completion of the T3 questionnaire. Following completion of the T1 questionnaire, participants will be randomised to view the intervention or control video.

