#### Assignment of interventions

##### Treatment allocation and concealment

All participant data will be collected and managed by an external data management contractor, Strategic Data Pty Ltd (now trading as Logicly). Allocation will be conducted using computer-generated random numbers using an automated data management system after completion of the T1 questionnaire. No stratification will be used.

The researchers, including the statistician responsible for the analysis of outcomes, will be blinded until after the completion of analysis to assess the primary outcome (comparing T1 and T2 data), which will take place after completion of T2. The study psychologist will also be unaware of any participant’s allocation unless they describe the video they have seen in the course of their interaction. If this were to occur, the psychologist would not reveal the participant’s allocation to the researchers.

Because they are aware of the content of the video they watch, it will not be possible to totally blind participants to their allocation. However, they will not be made aware that they could have been allocated to watch either an intervention or control video until T3. In the T3 questionnaire, we will explain the existence of the intervention and control group and ask participants to indicate the group to which they believe they have been assigned. Therefore, we will attempt to maintain the blinding of participants to the degree possible within this study design.

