### Participant timeline

After registering their interest in participation, participants will attend an online information session. After consenting, participants will immediately be given a link to complete the T1 questionnaire, which will include questions about socio-demographics, suicide risk, help-seeking intentions, intentions to encourage other males to seek help, male depression symptoms, self-reliance, health service use, and social support. Following completion of the T1 questionnaire, participants will be randomly assigned to intervention or control groups by the independent data management contractor. Immediately after randomisation, Strategic Data will email participants a link to their allocated online video (intervention or control); they will also receive a reminder to watch the video at day 3. They will be sent the video link again on day 7, along with the link to the T2 questionnaire. The T2 questionnaire will include questions about help-seeking intentions, intentions to encourage other males to seek help, self-reliance, social support, and feedback on the video. If participants do not view the video within 1 week of receiving the link or do not complete the T1 questionnaire, two reminder emails will be sent 10 and 12 days after T1. The link will expire after 1 week and participants will no longer be able to complete the T2 questionnaire. One month after T2, participants will be emailed the T3 questionnaire, which replicates the T1 questionnaire with the exceptions that it also includes questions about the effects of viewing the allocated video and does not include the DSI-SS. Participants will receive two reminders 3 and 5 days after the initial T3 email is sent. The link will expire after 1 week and participants will no longer be able to complete the T3 questionnaire. All participants who complete the T1 questionnaire will proceed to the T3 questionnaire, regardless of whether they complete the T2 questionnaire or watch their allocated video. See Fig. 1 for the timeline for the trial and Table 1 for the schedule of assessments.

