**Fig. 1 Fig1:**
[figure not shown]
Timeline for the trial. *Note:* DSI-SS, Depression Symptom Inventory—Suicidality Subscale [12]. See Table 1 for further information about T1, T2, and T3 questionnaires and timing

**Table 1 Tab1:** Schedule of assessments

Variable	Measure	Timeline		
		T1	T2	T3
*Screening measure*				
Suicide risk	Depression Symptom Inventory—Suicidality Subscale [12]	X		
*Primary outcome measure*				
Help-seeking intentions	General Help-Seeking Questionnaire—Self [13]	X	X	X
*Secondary outcome measures*				
Intentions to encourage other males to seek help	General Help-Seeking Questionnaire—Other [13]	X	X	X
Self-reliance	Conformity to Masculine Norms Inventory 30—Self-reliance subscale [14]	X	X	X
Male depression symptoms	Male Depression Risk Scale-7 [15]	X		X
Health service use	Health Service Use Questionnaire	X		X
*Other measures*				
Socio-demographics	Information about age, postcode, country of birth, language, marital status, current student, highest education, and employment	X		
Social support question	Information about the number of close friends and close relatives	X	X	X
Feedback on video	Information about video enjoyment, likeability, take-home message, degree of intended sharing with others, and belief about impact		X	
Effects of viewing the video	Information about life changes and time spent with friends			X

*Note.* T1, the T1 questionnaire is completed in the online information session; T2, the T2 questionnaire becomes available 7 days after completion of the T1 questionnaire and the survey expires after 1 week; T3, the T3 questionnaire is made available 4 weeks after the T2 questionnaire is completed or expires. The survey link expires after 1 week

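### The arm-specific video link goes out as soon as a man finishes T1, so early finishers may be able to open it while a mixed-arm group session is still running

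*Protocol article*

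**What the plan says.** The relevant statements are spread over several sections of the protocol article.

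- **Group setting.** Study setting: "They will attend an orientation session with up to nine other participants via the online web conferencing software, Zoom". Participant selection: "They must then attend an online orientation session run by one of our researchers and a study psychologist".
- **Where T1 is done.** Note to Table 1: "the T1 questionnaire is completed in the online information session".
- **When allocation happens.** Treatment allocation and concealment: "Allocation will be conducted using computer-generated random numbers using an automated data management system after completion of the T1 questionnaire". The same section adds "No stratification will be used".
- **When the video is sent.** Participant timeline: "Immediately after randomisation, Strategic Data will email participants a link to their allocated online video". Under Treatment adherence, the links can be used without limit until T2 is completed, and they are sent again on day 3 and day 7.
- **What the masking consists of.** Treatment allocation and concealment concedes that participants cannot be fully blinded, but says "they will not be made aware that they could have been allocated to watch either an intervention or control video until T3". Researchers are to stay blinded until the primary analysis is done. A psychologist who hears a man describe his video is not to pass this on to the researchers. The Discussion cites the researchers' blinding when it argues that social desirability bias should be equal in the two arms.

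**The concern.** Men finish a questionnaire at different speeds. With T1 done in the session, allocation triggered by its completion and the link sent at once, the trial itself creates a period in which one man may hold a playable, arm-specific video while others allocated to the other video, and the staff, are still connected.

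The men's only masking is that they do not know a comparison exists. The primary outcome is their own report of help-seeking intentions at T2. A control participant who has heard that others received a song about men talking could work out his role before he answers. The between-arm comparison of change removes social desirability only where it is the same in both arms, and unmasking need not act equally on both.

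Two features limit the protection in place. The stated rule for disclosure covers a man describing his video to the psychologist, and it does not help if the remark is made in a session that a researcher is also running. The question asking men to guess their arm comes at T3, whereas the primary and lack-of-net-harm analyses are run before T3 data are collected. A break in masking would therefore not be visible when the release decision is taken.

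**Working it through.** The plan gives no figure on this point, so there is none to reproduce. The check has two parts: the sequence of events, and the chance that a session contains both arms.

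**Sequence**

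1. Up to ten men (one plus up to nine others), a researcher and a psychologist are in the session (Study setting; Participant selection).
2. Each man completes T1 there (Table 1 note).
3. He is then allocated automatically and individually (Treatment allocation and concealment).
4. His link is emailed straight away (Participant timeline).
5. No section says when a man leaves the session, whether men can speak or chat after T1, or whether the video may be opened there. In-session viewing is neither required nor excluded.

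Steps 1 to 4 are stated. That an early finisher may hold the link while others are present follows from them. That he is in fact still connected, watches and comments does not.

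**Chance that a session is mixed**

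Inputs: 1:1 allocation of individuals, no stratification, session size k up to 10, total 446. Assumption: simple randomisation. The probability that all k men fall in one arm is 2 × 0.5^k, so

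P(both arms present) = 1 − 2 × 0.5^k

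| Men in session | 2 × 0.5^k | P(both arms present) |
|---|---|---|
| 10 | 0.0020 | 99.8% |
| 8 | 0.0078 | 99.2% |
| 5 | 0.0625 | 93.8% |
| 3 | 0.25 | 75% |
| 2 | 0.50 | 50% |

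With full sessions, 446 / 10 = 44.6, so at least 45 sessions are needed. The expected number containing only one arm is 45 × 0.00195 = 0.09. Practically every full session would be mixed; small sessions less often.

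**Reach of one disclosure**

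A disclosure in one full session reaches at most 10 men, or 10 / 446 = 2.2% of the sample. Turning this into a bias in the primary comparison would need the share of sessions with a disclosure and its effect on T2 answers in each arm. The article gives neither, so the calculation stops here.

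**The case against.** The strongest reply is that the key circumstance is inferred. The group discussion comes before consent and T1, no joint activity is described after T1, and a condensed article commonly leaves session logistics to the full protocol. Disclosure also needs a chain of unplanned events: a man stays online, notices the email, plays a four-minute video during the call and mentions it. Access lasts until T2 is completed, so nothing prompts him to watch then. This stands, and it rules out any statement that masking *will* break.

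Several stronger readings are tempting, and the article does not support them:

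- *That 94% to 99.8% of sessions are unmasked.* These figures are the chance that both arms are present, which is an ordinary result of randomising individuals.
- *That one remark tells the group there are two videos.* One remark describes one video. A listener learns that there are two only by comparing it with another, whether his own or another man's.
- *That T1 is biased between arms.* Men still answering T1 are not yet randomised, so any influence on them is balanced in expectation, and allocation concealment is intact.
- *That outcome assessment or analysis is unblinded.* Participants enter their own answers online, and nothing places the statistician in the session.

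It can also be said that the fix is partial. Snowball recruitment means that acquaintances may hold different videos and compare them during the week. That is true, but the session is mixed-arm contact that the trial arranges itself, and it is the part the trial can easily control.

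What the reply does not remove is that the article fixes the timing. The link is stated to go out at once, and T1 is stated to be done in the session. The point therefore concerns a stated choice and not a gap. That choice sits poorly with the aim, in Treatment allocation and concealment, of preserving participants' blinding as far as the design permits.

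**Conclusion.** The point holds as an avoidable risk in the stated procedure, not as a demonstrated failure of masking. Sending the link on completion of T1, inside a group session, allows a man to open an arm-specific video while men allocated to the other video and a researcher may still be present. No safeguard for that situation is stated.

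The only quantity that can be computed is how often a session is mixed: 99.8% for ten men and 93.8% for five, assuming simple 1:1 randomisation. One disclosure in a full session would reach at most 2.2% of the 446 men. The frequency of disclosure and the size or direction of any bias cannot be derived from the article, and a reader should not infer that the primary comparison is compromised. The case for acting is that the outcome is self-reported, participant masking is already partial, and the change is cheap.

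**What to change.** In the Participant timeline section, replace the immediate dispatch with a delayed one, for example: *Strategic Data's system will release the video links automatically at a fixed time after the orientation session has closed, with the same timing in both arms.* Randomisation can still follow completion of T1; only the email is held. If the system already works this way, the section should say so.

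The cost is a send-time setting at the data management contractor and a delay of some hours in first access, within a viewing period of about a week. A small loss of same-day viewing is possible. The day-3 reminder and the day-7 link are counted from T1 and do not change.

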**Fig. 1 Fig1:**
[figure not shown]
Timeline for the trial. *Note:* DSI-SS, Depression Symptom Inventory—Suicidality Subscale [12]. See Table 1 for further information about T1, T2, and T3 questionnaires and timing

**Table 1 Tab1:** Schedule of assessments

Variable	Measure	Timeline		
		T1	T2	T3
*Screening measure*				
Suicide risk	Depression Symptom Inventory—Suicidality Subscale [12]	X		
*Primary outcome measure*				
Help-seeking intentions	General Help-Seeking Questionnaire—Self [13]	X	X	X
*Secondary outcome measures*				
Intentions to encourage other males to seek help	General Help-Seeking Questionnaire—Other [13]	X	X	X
Self-reliance	Conformity to Masculine Norms Inventory 30—Self-reliance subscale [14]	X	X	X
Male depression symptoms	Male Depression Risk Scale-7 [15]	X		X
Health service use	Health Service Use Questionnaire	X		X
*Other measures*				
Socio-demographics	Information about age, postcode, country of birth, language, marital status, current student, highest education, and employment	X		
Social support question	Information about the number of close friends and close relatives	X	X	X
Feedback on video	Information about video enjoyment, likeability, take-home message, degree of intended sharing with others, and belief about impact		X	
Effects of viewing the video	Information about life changes and time spent with friends			X

*Note.* T1, the T1 questionnaire is completed in the online information session; T2, the T2 questionnaire becomes available 7 days after completion of the T1 questionnaire and the survey expires after 1 week; T3, the T3 questionnaire is made available 4 weeks after the T2 questionnaire is completed or expires. The survey link expires after 1 week

### Measures

#### Screening measure

The Depression Symptom Inventory—Suicidality Subscale (DSI-SS) is a 4-item self-report measure of suicide risk [12]. Scoring 2 or above on the DSI-SS will trigger a follow-up call from a study psychologist. Examples items include ‘Sometimes I have thoughts of killing myself’ (score = 1) and ‘In some situations, I have impulses to kill myself’ (score = 1). The DSI-SS has demonstrated good internal consistency; convergent validity with a range of measures, including hopelessness and lack of interpersonal belonging; and the ability to differentiate between people with and without suicide attempts [15]. Despite the established cut-point for suicide risk in the general population being 3, we have chosen 2 as the cut-off for follow-up assessment to minimise risk to participants.

#### Primary outcome measure

The General Help-Seeking Questionnaire—Self (GHSQ-Self) is a 13-item self-report measure of help-seeking intentions [13]. The GHSQ is a valid and reliable measure of intentions to seek help when experiencing personal difficulties [13]. The GHSQ-Self asks, ‘If you were having a personal or emotional problem, how likely is it that you would seek help from the following people or services?’ Ten responses are provided: *intimate partner*, *friend*, *parent*, *other family members*, *mental health professional*, *phone helpline*, *doctor*, *minister or religious leader*, *I would not seek help from anyone*, and *I would seek help from another not listed above*. We have modified this scale by providing an additional three responses: *online health chat rooms*, *online searches for health information*, and *social media*. Respondents rate the likelihood on a 7-point scale (1 = *extremely unlikely* to 7 = *extremely likely*); scores are summed, and a higher total score indicates greater intentions to seek help. The GHSQ is widely used and was used in our previous RCT of ‘Man Up’, discussed in the ‘Background’ section of this paper [11].

#### Secondary outcome measures

The General Help-Seeking Questionnaire—Other male (GHSQ-Other) is an adapted version of the GHSQ [13], and is a 13-item self-report measure of intentions to encourage other males to seek help. The GHSQ-Other format is as the GHSQ-Self above, with the variation that the question prompt asks: ‘If a male friend or family member of yours was having a personal or emotional problem, how likely is it that you would recommend to that person to seek help from the following people?’

The Conformity to Masculine Norms Inventory-30—Self-Reliance subscale (CMNI-30-SR) is a 3-item self-report measure of self-reliance [14]. The CMNI-30 assesses conformity to traditional masculine norms across 11 norms, including self-reliance. The self-reliance subscale relates to willingness to ask for help when needed. Participants rate their agreement (1 = *strongly disagree* to 3 = *strongly agree*) with three responses: ‘It bothers me when I have to ask for help’, ‘I never ask for help’, and ‘I am not ashamed to ask for help’. The subscale score is a sum of responses, with higher scores indicating higher levels of self-reliance.

The Male Depression Risk Scale-7 (MDRS-7) is a 7-item self-report measure of male-specific depression symptoms [15]. It assesses symptoms in six domains: emotion suppression, drug use, alcohol use, anger and aggression, somatic symptoms, and risk-taking. Each item is rated for how frequently the respondent has experienced that symptom over the last month (0 = *none of the time* to 3 = *all of the time*). Items can be summed to provide an overall depression score.

The Health Service Use Questionnaire (HSUQ) is a modified version of the self-report measure of the Resource Use Questionnaire [16] developed for use in this study. The HSUQ has eight items measuring health service use. These eight items will be used to assess participants’ use of a range of health services for mental health difficulties over the past 4 weeks. Use of a range of services is measured, including primary health services (e.g. consultations with a general practitioner, psychologist), inpatient admissions (e.g. hospital, community care unit), Internet-based services (e.g. information pages, online support group), and phone counselling. Use of psychotropic medications (e.g. sleeping tablets, antidepressants) is also assessed, as is the effect of mental health difficulties on functioning at work/in education.

#### Other measures

Social support will be measured by a single item measure, which reads: ‘About how many close friends and close relatives do you have (people you feel at ease with and can talk to about what is on your mind)?’ This item will be used in analyses using scores from the GHSQ-Self, to account for the possibility that low intentions to seek help may be related to a lack of availability of friends or relatives from whom participants can gain support.

At T2, we will ask participants a multiple-choice knowledge question about the content of the video to assess their attention to the video; we will ask them to rate from 1 (not at all) to 10 (very much) how much they enjoyed the video; and two open-ended questions about the parts they liked most and least; one open-ended question about the take-home message of the video. We will also ask them to indicate on a scale from 1 (no impact) to 10 (a great impact) the impact the video would have on men’s health and wellbeing.

At T3, we will ask participants different questions about the effects of the video. We will ask ten questions regarding whether the video has resulted in their changing their behaviour (e.g. spending more time with male friends), the parts of the video that had the most positive and negative impacts and their effects, whether they talked to others about the video and their likelihood of liking or sharing the video online. Some of these questions are closed ended (i.e. Yes/No) and some use rating scales (e.g. 1 (No, not at all) to 10 (Yes, a lot)). Others ask for explanatory free-text comments (e.g. Now tell us in your own words what were the parts of the video, if any, that had the most positive impact on you and explain why). We will also ask whether the participant believes they were allocated to the intervention or control group, after a brief explanation of the meaning of these conditions.

A copy of the full set of measures can be supplied upon reasonable request to the corresponding author.

